### Outcome measures (dependent variables)

We chose the KOS-ADLS as the primary outcome to monitor clinical improvement. Secondary outcomes include VASs, a Global Rating of Change (GRC) question, as well as lower limb isometric muscle strength and running kinematics and kinetics.

#### Knee outcome survey – activities of daily living scale

A systematic review pertaining to self-reported questionnaires used in individuals with PFP recommended the KOS-ADLS over other knee-specific scales based on its psychometric properties and clinical applicability for runners [40]. The KOS-ADLS is a 14-item knee-specific questionnaire that evaluates symptoms and functional limitations experienced during activities of daily living in individuals with various knee disorders [41]. The validated French version of the KOS-ADLS will be used (MDC90 = 8.3 points; CID = 13.6 points) [36].

#### Visual analog scales

Knee pain will be assessed with VASs for usual pain, worst pain and pain during running. These VASs were shown to be reliable and responsive in runners with PFP [36].

#### Running mileage

Runners’ training will be monitored using a GPS-enabled Garmin Forerunner 15 watch. Weekly running mileage will be made available to researchers using an online log, and will allow us to assess changes in training volume during the 8 week intervention.

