### Procedures

All included runners will take part in the baseline evaluation session. First, questionnaires on sociodemographic, symptomatology, comorbidity, and running habits will be completed. Thereafter, the level of symptoms and functional limitations will be evaluated using self-reported questionnaires (KOS-ADLS and visual analog scales), before assessing knee and hip muscle strength. Then, lower limb kinematics and kinetics will be evaluated while running on an instrumented treadmill. Finally, runners will be randomly assigned to one of the three intervention groups, and will take part in their assigned 8 week rehabilitation program.

At weeks 4, 8, and 20 (3 months following completion of the program), self-reported questionnaires completed at baseline will be re-administered. This will allow us to determine if a program leads to a faster recovery and to better long-term effects. At week-8 evaluation, lower limb mechanics during running and strength will also be revaluated in the laboratory. All runners will be provided with a GPS-enabled watch (Garmin Forerunner 15) so that running mileage, speed, duration and step count are monitored during the intervention period.

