### Rehabilitation programs (independent variables)

Each runner will take part in one of three rehabilitation programs carried out over five sessions by independent physiotherapists. A training session will be performed prior to recruitment to ensure standardisation of the intervention between the physiotherapists, and detailed documents reviewing the content of each meeting will be provided. Furthermore, frequent follow-ups will be made by the research team with the physiotherapists to ensure the consistency of program delivery. Runners will receive written instructions, and, when applicable, pictures illustrating the exercises. All components of each intervention will be addressed at every visit to the clinic. During the programs, participants will continue to run.A)*Education group*This group will receive a program that will only include the same education component on symptoms management that the two other groups will receive. Runners will be asked to run more often, but to decrease daily distance and running speed as well as to avoid downhill running. They will be instructed to maintain patellofemoral pain level at a maximum of 2/10 during running. In addition, pain should return to before-training levels within 60 min post training. Gradually, running distance will be increased according to symptoms, up to baseline level or more, before adding speed and hills [30].B)*Exercise group* (strengthening and lower limb control)In addition to the education on symptoms management, runners will be asked to perform a standardised exercise program focusing on strengthening and lower limb control three times per week. The same exercise program was used in a previous study from our research group [30]. Each exercise session will last a maximum of 20 min. Exercises will be gradually progressed through higher difficulty levels of knee/hip/core strength and lower limb control including jumps and elastic bands. Exercises will be individually dosed and progressed by the treating physiotherapist. No recommendation about lower limb alignment during running will be provided.C)*Gait retraining group* (reducing impact forces)In addition to education on pain management, runners will receive personalised advice on running mechanics in order to reduce patellofemoral joint load. Specifically, step rate will be increased, and noise produced during running will be decreased so that vertical ground reaction forces are reduced [28, 29, 49–51]. Runners for whom noise reduction will not be an efficient strategy will be asked to modify their foot strike pattern to midfoot or forefoot [31]. We decided to use the approach targeting decreased ground reaction forces since it is applicable to a vast majority of runners, compared with the kinematics approach which has only been tested in runners with excessive hip adduction [32, 34].

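### Running mileage is analysed as change within the 8 weeks with no pre-randomisation reference, so its Time effect may mostly show the prescribed cut and rebuilding of distance

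*Protocol article*

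**What the plan says.** The abstract of the protocol article lists running mileage as a secondary outcome. Four statements determine how it is measured and analysed.

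- **Recording window.** Under Procedures, runners receive a GPS watch "so that running mileage, speed, duration and step count are monitored during the intervention period". No recording before the intervention is described.
- **Purpose.** Under Running mileage, the weekly log "will allow us to assess changes in training volume during the 8 week intervention".
- **Test.** The sample size and statistical analyses paragraph puts mileage into the same two-way ANOVA (Groups x Time) as KOS-ADLS and the pain scales. It does not give the time levels for mileage.
- **Instruction acting on the outcome.** Under Rehabilitation programs, the education component reads: "Runners will be asked to run more often, but to decrease daily distance and running speed as well as to avoid downhill running". Later, "Gradually, running distance will be increased according to symptoms, up to baseline level or more, before adding speed and hills". This is "the same education component on symptoms management that the two other groups will receive", so it applies to all three arms.

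Two sources could supply a pre-randomisation value. Eligibility requires at least 15 km per week, and at the baseline session "questionnaires on sociodemographic, symptomatology, comorbidity, and running habits will be completed". The article does not say that either yields a weekly distance for the analysis.

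**The concern.** KOS-ADLS and the pain scales are measured at baseline, before randomisation, so Time in their ANOVA starts from an untreated level. For mileage, the text describes only watch data from the intervention period. Those weeks fall under an instruction that acts directly on distance, first downward and then upward.

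Three readings of the result are at stake.

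- A rise over the 8 weeks could be reported as a training gain when runners have only returned to where they started.
- A program that lets its runners keep more distance from the first week onward, by a constant amount, would produce no interaction.
- If the arms cut by different amounts early on, the arm that cut most shows the largest increase and could be misread as the one that gained most.

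The education component takes the runner's own baseline level as its yardstick. Change within the 8 weeks does not measure against it.

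**Working it through.** **Inputs.** The article gives no mean, SD or target difference for mileage, so there is no mileage figure to reproduce. Its 20 per group is for KOS-ADLS: a two-sample t-test with difference 13.6, SD 12.9, two-sided alpha 0.05 (sidedness assumed) and 90% power gives 19.9, so 20. That number serves below only as a group size. All mileage values are assumptions: mean 22 km per week, between-runner SD 7, within-runner SD 5, 8 weekly values, 3 arms of 20. The first-week drop is 0 or 6.6 km (30% of 22), with linear return to the usual level by week 8.

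**Step 1: what enters Time and what enters the interaction.** Split-plot ANOVA, 4,000 simulated trials per row:

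| Scenario | Groups x Time rejects | Time rejects | Mean change, week 1 to week 8 |
|---|---|---|---|
| No drop | 5.3% | 4.7% | 0.0 km |
| Same 6.6 km drop in all arms, full return | 4.7% | 100% | +6.6 km |
| One arm drops 4 km more, all arms return fully | 32% | 100% | +7.9 km |

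In the second row, net change from usual distance is zero, yet Time is always significant. The interaction keeps its nominal 5%.

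**Step 2: unequal early cuts.** In the third row, the arm that cut most rises by 6.6 + 4 = 10.6 km and the others by 6.6 km, although week-8 distance is the same in all three. As percentages of pre-trial distance (assumed values): 50 to 90 is +40 points and 70 to 90 is +20. The 20-point contrast in change goes with a week-8 difference of 90 - 90 = 0. With linear return the 8-week averages are (50 + 90)/2 = 70 and (70 + 90)/2 = 80, so the Group effect favours the arm that cut less.

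**Step 3: a constant difference.** With the same kind of assumed values, let one arm go from 70 to 90 and another from 50 to 70. The changes are 90 - 70 = 20 and 70 - 50 = 20, so the interaction is zero. The averages are 80 and 60, and only the Group main effect shows the 20-point difference.

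**Step 4: the Group effect without adjustment.** A runner's 8-week mean has variance 7² + 5²/8 = 49 + 3.1 = 52.1, of which 49/52.1 = 94% is stable difference between runners. The standard error of a difference between two arms of 20 is √(2 × 52.1/20) = 2.28 km. A pre-randomisation covariate correlated r with that mean removes r² of the variance: 36% at r = 0.6 and 64% at r = 0.8 (assumed range). The standard error then falls to 2.28 × √(1 - 0.36) = 1.83 km or 2.28 × √(1 - 0.64) = 1.37 km.

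**Step 5: is a lower weekly distance certain?** No. Runners are also asked to run more often. Going from 3 to 4 runs leaves weekly volume unchanged if each run is 1 - 3/4 = 25% shorter; going from 3 to 5 runs does so at 1 - 3/5 = 40%.

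**The case against.** A reader might infer that the Groups x Time test itself measures rebound from an imposed reduction. The documents do not support that. The instruction is common to all three arms, and Step 1 shows that a common cut goes into Time and cancels from the interaction. Nor does any section make week 1 the baseline or specify a week-8-minus-week-1 score; a two-way ANOVA also has a Group effect, which retains an early advantage.

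If early cuts do differ by arm, they are real post-randomisation differences between programs. The 32% in Step 1 is correct detection of differing trajectories, not false positives; only its reading as a greater gain would be wrong. The fall in weekly distance is itself plausible rather than stated. It would also be too much to say that pre-trial distance is known and ignored, because the content of the running-habits questionnaire is not given. The hypothesis of faster improvement concerns symptoms and function, so it does not bear directly on mileage.

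Finally, this is a condensed article, and time levels and covariates for a secondary outcome are commonly left to the analysis plan. Silence on those is no fault.

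All of this stands, and it limits the point. It does not remove it, because the article does fix a recording window confined to the intervention and a purpose defined as change within it. The planned ANCOVA does not fill the gap either: it applies only if baseline characteristics turn out to differ, and it does not name mileage.

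**Conclusion.** The point holds in a limited form. As described, the mileage analysis has no pre-randomisation reference, so its Time effect and within-group increases cannot be separated from the prescribed reduction and rebuilding. The randomised Groups x Time comparison is not invalidated. It is blind to a difference that starts in the first week and stays constant, and it is open to misreading if the arms cut by different amounts. The Group effect that would show a constant difference is unadjusted for usual distance.

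The size cannot be taken from the documents. The 6.6 km apparent growth, the 20-point contrasts, the 32% rejection rate and the 36% to 64% variance reduction all come from assumed values. The conclusion about Time also assumes that weekly distance does fall early on. This is a worthwhile, inexpensive improvement to a secondary outcome; the primary KOS-ADLS analysis is untouched.

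**What to change.** In the statistical analyses paragraph, or in the analysis plan if one exists:

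1. State that every watch-recorded week is a post-randomisation outcome and name the time levels.
2. Include pre-randomisation weekly distance, from screening or the running-habits questionnaire, as a covariate regardless of whether the groups differ at baseline.
3. Report both the Group effect and Groups x Time, and do not interpret an interaction as a greater gain without showing the early weeks.
4. Report week-8 distance relative to pre-trial distance, by group. This answers whether runners are back at their own level, which the covariate alone does not.

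The cost is about two sentences, plus confirmation that weekly kilometres are recorded before randomisation. The downside is a self-reported covariate beside a watch-recorded outcome. Because it is collected before allocation, its error costs some precision but does not bias the randomised comparison. The ratio in item 4 mixes two instruments, so its absolute level needs more caution than the contrast between arms.

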#### Lower limb isometric strength

Strength will be assessed by producing maximal voluntary isometric contraction of knee extensors, hip external rotators, abductors and extensors using a Medup handheld dynamometer (Atlas-Medic, Quebec City, Canada) as per validated methods [42]. Non-elastic straps will be used to secure participants’ position and limbs during testing. The peak force value (kg) from three trials will be considered and normalised in percentage of bodyweight [43, 44].

#### Lower limb kinematics and kinetics

Lower limb mechanics of the affected leg during running will be evaluated using kinematic and kinetic data. Rigid non-colinear triads of reflective markers will be placed over the cervicothoracic and lumbosacral junctions as well as bilaterally on the lateral part of the foot, shank and thigh. Triads attached to the thighs will be made of custom-molded thermoplastic, and securely attached using Velcro straps to minimize movement artefacts. Anatomical markers will be temporarily installed for a standing calibration trial at the anterior and posterior tips of the shoes, lateral head of the fifth metatarsals, medial and lateral malleolli, medial and lateral femoral condyles, iliac crests, anterior superior iliac spines and lateral tip of the acromion. Kinematic data will be collected at 200 Hz using an 8-camera VICON MX-T motion capture system and VICON Nexus software (VICON motion systems, CA, USA). All participants will start by running on an instrumented treadmill (Bertec Corp, Columbus, OH) during 5 min to ensure consistency of running kinematics. To reproduce individual training conditions, runners will wear their usual running shoes and will select their preferred running speed between eight and 10 km/h (same shoes/speed for weeks 0 and 8) [45]. Running data will then be collected during the following 3 min.

Kinematic variables of interest will be hip adduction, hip internal rotation as well as contralateral pelvic drop excursions and peak angles during the stance phase [19, 20]. Kinetic variables of interest will include the vertical loading rate [46], and maximum vertical ground reaction force. In addition, Newton–Euler inverse dynamics equations will be used to estimate the shear and compression reaction forces within the sagittal plane at the patellofemoral, tibiofemoral, and ankle joints [47, 48].

### Rehabilitation programs (independent variables)

Each runner will take part in one of three rehabilitation programs carried out over five sessions by independent physiotherapists. A training session will be performed prior to recruitment to ensure standardisation of the intervention between the physiotherapists, and detailed documents reviewing the content of each meeting will be provided. Furthermore, frequent follow-ups will be made by the research team with the physiotherapists to ensure the consistency of program delivery. Runners will receive written instructions, and, when applicable, pictures illustrating the exercises. All components of each intervention will be addressed at every visit to the clinic. During the programs, participants will continue to run.A)*Education group*This group will receive a program that will only include the same education component on symptoms management that the two other groups will receive. Runners will be asked to run more often, but to decrease daily distance and running speed as well as to avoid downhill running. They will be instructed to maintain patellofemoral pain level at a maximum of 2/10 during running. In addition, pain should return to before-training levels within 60 min post training. Gradually, running distance will be increased according to symptoms, up to baseline level or more, before adding speed and hills [30].B)*Exercise group* (strengthening and lower limb control)In addition to the education on symptoms management, runners will be asked to perform a standardised exercise program focusing on strengthening and lower limb control three times per week. The same exercise program was used in a previous study from our research group [30]. Each exercise session will last a maximum of 20 min. Exercises will be gradually progressed through higher difficulty levels of knee/hip/core strength and lower limb control including jumps and elastic bands. Exercises will be individually dosed and progressed by the treating physiotherapist. No recommendation about lower limb alignment during running will be provided.C)*Gait retraining group* (reducing impact forces)In addition to education on pain management, runners will receive personalised advice on running mechanics in order to reduce patellofemoral joint load. Specifically, step rate will be increased, and noise produced during running will be decreased so that vertical ground reaction forces are reduced [28, 29, 49–51]. Runners for whom noise reduction will not be an efficient strategy will be asked to modify their foot strike pattern to midfoot or forefoot [31]. We decided to use the approach targeting decreased ground reaction forces since it is applicable to a vast majority of runners, compared with the kinematics approach which has only been tested in runners with excessive hip adduction [32, 34].

Sample size calculation and statistical analyses: Sample size calculation is based on changes to KOS-ADLS scores, our primary outcome, which are expected to increase following the different interventions. In a previous study using an 8 week multimodal intervention program similar to the current study, KOS-ADLS scores increased from 71.7 ± 12.9 to 89.5 ± 11.9 [30]. Considering similar score changes to our primary outcome, α = 0.05, power of 90 % and CID of 13.6 points for the KOS-ADLS, 20 runners are needed in each group (G*Power 3.1.7). When adding an anticipated attrition rate of 15 %, 23 runners per group are needed; therefore, a total of 69 runners will be recruited. Baseline demographic data will be compared (one-way ANOVA and Chi-squared tests). If baseline characteristics are different across groups, we will adjust group comparisons for confounding variables using an ANCOVA model. An intention-to-treat analysis will be used in which all participants will be analysed in the group to which they were originally assigned, up to the 8 week point. Dropouts or loss to follow-up will not be carried forward to the 3 month follow-up, since a successful outcome after 8 weeks may not necessarily be maintained 3 months later. This will avoid false assumptions regarding durable benefits from the intervention. Per protocol analyses (i.e., analyses restricted to patients who received the intervention as intended) will also be performed. All dropouts and reasons underlying dropouts will be reported. If requested, subjects electing to drop-out will be referred to their treating physician for other treatment options. Any harms or unintended effects during the course of the rehabilitation programs will be reported and discussed. For objective one, a 2-way ANOVA (Groups x Time) will be used to analyse the effects of the rehabilitation programs on KOS-ADLS, VASs and running mileage. For objective two, logistic regression analyses will be performed to identify if changes in running mechanics or strength are determinants of clinical success. For these analyses, results to KOS-ADLS will be dichotomised to changes equal or superior to the CID of 13.6 points, or to changes inferior to this value [36]. Subjective success will also be dichotomised to GRC ≥ +5 or GRC < +5.

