### Participants

Sixty-nine recreational runners with PFP will be recruited through advertisements in running events and sports medicine clinics in Quebec City, Canada, as well as through emails sent to Laval University students and employees. To be included, potential participants will have to meet the following inclusion criteria: 1- age between 18 and 45 years; 2- run at least 15 km per week; 3- present a history of anterior knee pain for at least 3 months; 4- report a pain level of at least 3/10 on a visual analog scale during running and during at least three activities among: kneeling, squatting, stairs and resisted knee extension [35]; and 5- score lower than 85/100 on the Knee Outcome Survey – Activities of Daily Living Scale questionnaire (KOS-ADLS), to ensure a minimum level of symptoms and limitations (clinically important difference of 13.6 points) [36]. In addition, runners will be excluded if they present one of the following conditions: 1- history of lower limb surgery or patellar dislocation; 2- pain believed to originate either from meniscus [37, 38] or from patellar tendon [39]; 3- pain following an acute trauma; 4- concurrent lower limb injuries; 5- history of neurological, inflammatory or rheumatoid disease. A member of the research team will perform a preliminary screening of the inclusion and exclusion criteria and explain the study during a telephone call. If they agree to participate, potential participants will then be met by a physiotherapist to confirm the diagnosis of PFP using the clinical tests. Ethics approval was obtained from the Institutional Review Board of Quebec Rehabilitation Institute (#2014-367), and all subjects will sign a detailed consent form before entering the study.

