### Randomisation/blinding

A randomisation list will be generated by an independent research assistant (not involved in data collection) using a computer random number generator. Allocation will be concealed in sequentially numbered sealed opaque envelopes. Given the influence of gender and foot strike pattern on lower limb mechanics during running, randomisation will be stratified to ensure balance of the treatment groups with respect to these variables (male/female; rearfoot strikers/non-rearfoot strikers). A block randomisation will also be used to make sure that three equal groups of 23 runners are obtained. Given that it is impossible to blind the treating physiotherapists and the runners, a single-blind design will be used, in which the evaluator will be blinded. Participants will be instructed not to discuss the specific program received with the evaluator.

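### The allowance for 15% attrition is slightly short: 23 runners per group leaves 19.55, not the 20 the power statement needs

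*Protocol article*

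**What the plan says.** The derivation is in the protocol article, in the paragraph on sample size calculation and statistical analyses that closes the section Rehabilitation programs (independent variables). It cites an earlier study of a similar 8 week programme, in which "KOS-ADLS scores increased from 71.7 ± 12.9 to 89.5 ± 11.9". The requirement is then given as "α = 0.05, power of 90 % and CID of 13.6 points for the KOS-ADLS, 20 runners are needed in each group". The next sentence applies an expected attrition of 15% and concludes that "23 runners per group are needed; therefore, a total of 69 runners will be recruited".

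The result is used elsewhere without change. Participants says "Sixty-nine recreational runners with PFP will be recruited", Randomisation/blinding uses blocks so that "three equal groups of 23 runners are obtained", and the Abstract also gives sixty-nine. No formula for the attrition allowance appears anywhere.

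The same paragraph describes an intention-to-treat analysis by assigned group that runs to week 8. It says that dropouts are not carried forward to the follow-up three months later, and it adds a per-protocol analysis.

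**The concern.** An attrition rate is a fraction of those randomised. To end with 20 after losing 15%, one divides 20 by 0.85 and rounds up. Adding 15% of 20 to 20 treats the rate as a fraction of the completers and gives too small a number. The article therefore prints three figures (20 needed, 15% lost, 23 randomised) that do not quite agree. What is at stake is a derivation that any reader can check, which sets both the recruitment target and the group size in the randomisation, and a stated power that is narrowly missed at the planned attrition.

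**Working it through.** **Inputs from the article.** Difference 13.6 points on the KOS-ADLS, alpha 0.05, power 90%, 20 per group before attrition, attrition 15%, 23 per group and 69 in total after attrition. The earlier study gives two SDs, 12.9 at baseline and 11.9 after the programme.

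**Assumptions.** The article does not name the test, its sidedness or the planning SD. I assume a two-sided two-sample t-test.

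**Step 1: reproduce the 20.** With SD 12.9, d = 13.6 / 12.9 = 1.054, and solving for 90% power gives n = 19.92, so 20 per group. The midpoint SD of 12.4 gives 18.5, so 19. SD 11.9 gives 17.1, so 18. Of these three, only SD 12.9 returns the stated figure, so I use it below.

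**Step 2: reproduce the 23.**
- 20 x 1.15 = 23.0, and 3 x 23 = 69.
- 20 / 0.85 = 23.53, which is 23 if rounded down.

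Both routes give the printed number.

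**Step 3: apply the 15% to those randomised.**
- 23 x 0.85 = 19.55 per group; 69 x 0.85 = 58.65 in total, against 60 needed.
- 24 x 0.85 = 20.4 per group; 72 x 0.85 = 61.2 in total.
- The largest loss from 23 that still leaves 20 is 3 / 23 = 13.0%. A fourth loss is 4 / 23 = 17.4% and leaves 19.

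The smallest group size that meets the target is thus 24, or 72 in total. Rounding up only the total gives 60 / 0.85 = 70.6, so 71, which does not divide into three equal groups.

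**Step 4: effect on power.** Noncentral t, SD 12.9, noncentrality = d x sqrt(n / 2), df = 2n - 2.

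| Completers per group | Noncentrality | Power |
|---|---|---|
| 20 | 3.334 | 90.1% |
| 19.55 | 3.296 | 89.4% |
| 19 | 3.249 | 88.5% |

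The loss is 90.1 - 89.4 = 0.7 points at the planned attrition, and 90.1 - 88.5 = 1.6 points if only 19 complete. With 19 completers, power is 90.8% at SD 12.4 and 92.9% at SD 11.9.

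**The case against.** Most of the case on the other side concerns size, and much of it stands.

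- **Rounding.** 15% of 23 is 3.45. No whole number of dropouts equals it, and the nearest, 3, leaves exactly 20. Over the whole trial, 15% of 69 is 10.35; ten dropouts leave 59 of the 60 needed. This is correct, and it shows how narrow the miss is. A planned rate should still be covered by rounding up.
- **The shortfall is not a whole runner per group.** A reader might set 69 against 72 and infer that the trial ends three evaluable runners short. That is the gap between recruitment targets. At the planned attrition the expected deficit is 20 - 19.55 = 0.45 per group, or 60 - 58.65 = 1.35 in total.
- **Power.** A reader might take 88.5% as the power under the plan. It needs 19 completers per group, which is 17.4% attrition rather than 15%.
- **Unstated inputs.** The power figures rest on a test and an SD that the article does not name, and the planned analysis is a Groups x Time ANOVA. With the smaller SDs power stays above 90% at 19 completers. However, those SDs do not give the 20 that the article says it needs.
- **Intention-to-treat.** The text implies that dropouts stay in the analysis up to week 8. If so, 23 per group enter it, and power at SD 12.9 would be 93.8% if imputed values counted as full information, which is optimistic. This limits where the shortfall applies but does not remove it. Carrying forward is ruled out for the last follow-up, the Abstract lists week 20 among the primary outcome's time points, and a per-protocol analysis is planned.
- **Origin of the 23.** A reader might infer that the authors certainly multiplied by 1.15. The exact match makes this likely, but rounding 23.53 down gives the same number, and the article does not settle it. The conclusion is the same either way.

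**Conclusion.** The attrition step is wrong as written. With 15% loss, 23 per group does not leave 20, and nothing else in the article corrects it. The miss is 0.45 of a runner per group, worth about 0.7 points of power under the assumed two-sided t-test with SD 12.9, or 1.6 points if only 19 complete. It bears mainly on week 20, the observed data and the per-protocol analysis.

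A reader might go further and infer that the trial is materially underpowered because of this step. The article does not support that: power stays within two points of the stated 90% even with 19 completers, and week 8 intention-to-treat appears to keep all those randomised. This is a minor correction to a stated calculation, and it gives no reason to doubt the design.

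**What to change.** Keep 69 and change one sentence in the sample size paragraph. Either of these is accurate:

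- 23 runners per group allows for about 13% attrition (3 of 23) while keeping the 20 needed; or
- attrition of 15% from 23 per group leaves 19 to 20 per group and about 89% power, with the test and SD behind that figure named.

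The cost is one sentence, with no change to recruitment or randomisation. The alternative is to raise the target to 24 per group (72 in total). That costs three more runners and matching edits in the Abstract, Participants and Randomisation/blinding. The small gain in power does not require it.

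### ANCOVA is used only if the groups happen to differ at baseline, so the primary model depends on the data and will usually forgo regression adjustment for baseline KOS-ADLS

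*Protocol article*

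**What the plan says.** The analysis text is the paragraph on sample size and statistical analyses, which closes the section Rehabilitation programs (independent variables).

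- Baseline testing: "Baseline demographic data will be compared (one-way ANOVA and Chi-squared tests").
- Adjustment rule: "If baseline characteristics are different across groups, we will adjust group comparisons for confounding variables using an ANCOVA model".
- Default analysis under the first objective: "a 2-way ANOVA (Groups x Time) will be used to analyse the effects of the rehabilitation programs on KOS-ADLS, VASs and running mileage". No covariate is named.
- Primary outcome (Outcome measures): "We chose the KOS-ADLS as the primary outcome to monitor clinical improvement".
- Baseline measurement (Procedures): at the baseline session, before random assignment, "the level of symptoms and functional limitations will be evaluated using self-reported questionnaires (KOS-ADLS and visual analog scales").
- Randomisation/blinding: the list is computer-generated, allocation is concealed in opaque envelopes, and randomisation is stratified by gender and foot strike pattern.

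The article gives no criterion for when groups count as different and no list of candidate covariates. It mentions tests only for demographic data.

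**The concern.** With concealed random allocation, any baseline difference between groups has arisen by chance. A test of that difference says nothing about whether the variable predicts KOS-ADLS at follow-up, and prediction is the reason to adjust. A rule that adjusts only when groups look different has three consequences:

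- The form of the primary comparison is settled after baseline data are seen. With no criterion or covariate list, the analyst has discretion.
- Baseline KOS-ADLS, a natural candidate for a prognostic covariate because it is the outcome measured earlier, will usually not be adjusted for by regression. If only demographic variables count, it may never trigger adjustment.
- Gender and foot strike are balanced by stratification, so they will rarely look different. The rule will normally leave out the very factors on which randomisation was restricted.

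At stake are prespecification of the primary analysis and precision, in a trial planned on 20 evaluable runners per group.

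**Working it through.** **Inputs from the protocol article.** SDs: "KOS-ADLS scores increased from 71.7 ± 12.9 to 89.5 ± 11.9". Target and size: "power of 90 % and CID of 13.6 points for the KOS-ADLS, 20 runners are needed in each group", with α = 0.05 (two-sided assumed). Attrition: "When adding an anticipated attrition rate of 15 %, 23 runners per group are needed". MDC90 = 8.3 points (section on the KOS-ADLS).

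**Assumptions.** The baseline-to-follow-up correlation r is not given, so r = 0.3, 0.5 and 0.7 are shown. SD is 12.9 at both times.

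**1. The plan's own figure.** A two-sample comparison of 13.6 points with SD 12.9, two-sided α 0.05 and 90% power needs 19 per group by the normal approximation and 20 by the noncentral t. The stated 20 reproduces, and 20 × 1.15 = 23.

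**2. What the default does with baseline.** Baseline is one level of Time, so the interaction compares changes from baseline. For a single follow-up visit with equal variances:

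- change score: SD × √(2(1 − r))
- ANCOVA: SD × √(1 − r²)
- variance ratio, change to ANCOVA: 2(1 − r)/(1 − r²) = 2/(1 + r)

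Power is for 20 per group and 13.6 points (noncentral t):

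| r | Change SD | ANCOVA SD | Variance ratio | Power, change | Power, ANCOVA |
|---|---|---|---|---|---|
| 0.3 | 15.26 | 12.31 | 1.54 | 78% | 93% |
| 0.5 | 12.90 | 11.17 | 1.33 | 90% | 96% |
| 0.7 | 9.99 | 9.21 | 1.18 | 99% | 99.5% |

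At r = 0.5 the change SD equals the raw SD (√(2 × 0.5) = 1), so the change score has the power the plan calculated. Below that it falls short; above it, it does better.

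**3. How often the rule would act.** If different means p < 0.05 (an assumption), one test triggers in 5% of trials. Baseline KOS-ADLS, if tested at all, would then go unadjusted in about 95%. With k independent tests, the chance of at least one trigger is 1 − 0.95^k: 23% for k = 5, 34% for k = 8, 40% for k = 10 and 54% for k = 15. The article does not fix k.

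**4. Behaviour of the two-stage rule.** Simulation: three arms of 20, baseline plus one follow-up, 40,000 runs. ANCOVA is used if the baseline F-test on KOS-ADLS has p < 0.05, and the change score otherwise.

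| | r = 0.3 | r = 0.5 | r = 0.7 |
|---|---|---|---|
| Type I error, two-stage | 4.3% | 4.4% | 4.7% |
| Power, one arm better by 8.3: two-stage | 39% | 53% | 76% |
| Same, ANCOVA always | 56% | 65% | 82% |
| Power, one arm better by 13.6: two-stage | 82% | 93% | 99.5% |
| Same, ANCOVA always | 95% | 98% | 99.8% |

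**5. Chance imbalance the rule leaves alone.** In simulated trials with a non-significant baseline test (3 × 20, SD 12.9), the baseline gap between two given arms has median 2.7 points and 95th percentile 7.3. A gap g shifts the expected difference in change by (1 − r) × g. At r = 0.5 that is 2.7 × 0.5 = 1.35 points at the median and 7.3 × 0.5 = 3.65 at the 95th percentile.

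**The case against.** Several points on the other side stand.

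- **The default is valid.** A reader might infer that the rule biases the comparison or inflates type I error. The calculations do not support this. Under randomisation a change comparison is unbiased over repeated trials, and the mechanical two-stage rule simulated at 4.3% to 4.7%, slightly conservative. Free choice of covariates after seeing the data could do worse, but that was not simulated and the article does not announce it.
- **Baseline KOS-ADLS is not ignored.** It enters as a level of Time. What is forgone is regression adjustment.
- **The trigger is partly inferred.** The article does not say that baseline KOS-ADLS is tested, gives no p-value threshold, and limits adjustment to confounders. It does not say that every variable with a significant test enters the model.
- **The planned power often survives.** At r of about 0.5 or more, the change score reaches 90%. The sample size is itself framed in terms of KOS-ADLS changes, so a change-type analysis fits it, and this point does not make the 20 per group wrong.
- **The ratio is for one contrast.** KOS-ADLS is measured at four times, and the overall interaction test is not a single change score.
- **The imbalance effect is modest.** Even the 95th-percentile shift of 3.65 points at r = 0.5 is below the MDC90 of 8.3 and the CID of 13.6.

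One defence does not stand: that this is detail left to a fuller plan. A condensed article may omit the covariate list, but here it states the conditional rule itself, and a plan that followed it would inherit the problem.

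**Conclusion.** The point holds as one of prespecification and efficiency. The article lets observed baseline differences decide whether the primary comparison is adjusted, and its default omits regression on a baseline measure already collected. For a single contrast, that default has 1.18 to 1.54 times the variance of ANCOVA for r between 0.7 and 0.3. Power for 13.6 points at 20 per group is 78% to 99%, against 93% to 99.5%; the planned 90% is missed only if r is below about 0.5. These figures rest on an assumed r, equal SDs of 12.9, two-sided α and a single follow-up visit. There is no demonstrated bias, error inflation or sample size error. It should be fixed, but it is not a fatal flaw.

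**What to change.** Remove baseline tests as a trigger for adjustment. They may remain as description, although summaries by group are enough. State in advance that KOS-ADLS at weeks 4, 8 and 20 is compared between groups with baseline KOS-ADLS, gender and foot strike pattern always as covariates, whatever the baseline data show. A mixed model with group, time and group x time would do this. Analyse each VAS the same way, with its own baseline value.

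The cost is a change of wording in the protocol or analysis plan. No extra data, visits or runners are needed. It should be made before outcome data are examined, because a covariate set chosen afterwards would not remove the concern.
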